### Sample size analysis

In the literature, the incidence of MACE after cardiac surgery varies between 11 and 40%. The primary end-point in the present study, composite MAE, is broader than MACE and includes the latter. In a previous cohort study at the study site (Helsinki University Hospital, Meilahti hospital) the incidence of MAE was 30%. Thus, this incidence was used in the sample size analysis. Originally, it was estimated that 621 patients per group would be required to detect a 7.5%-unit absolute difference between the study groups in the primary outcome measure (proportion of patients with at least one MAE) with a two-sided significance level α = 0.05, and power of 80%. Accordingly, the original sample size was 1250 patients.

A predefined confirmatory analysis of incidence of MAE among the first 550 patients was performed for potential adaptation of the sample size in order to preserve the 80% power to detect a 7.5%-unit absolute difference between the study groups. The MAE incidence after 550 patients was 42%. In empirical analysis (without breaking the allocation code) the assumption of 50% and 42.5% MAE incidence in the two study groups turned out to be the “worst case scenario” (i.e., the highest needed patient number) with an estimate of 693 patients required for both patient groups. In accordance with the new power analysis, the sample size was increased by 2 × (693 − 1250/2) = 136 patients. Hence, the final adapted sample size will be 1250 + 136 = 1386. The Data and Safety Monitoring Board (DSMB) approved the extension of sample size and a decision was made before the interim analysis of 600 patients. Withdrawn patients or those who drop out, for whom the primary endpoint cannot be assessed, will be replaced.

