## Methods/design

### Patients

This study will be a double-blind, randomized, controlled trial in 1386 cardiac surgery patients scheduled for elective surgery or operated on during the index admission in Helsinki University Hospital, Helsinki, Finland. The patients will be allocated 1:1 into the two study groups.

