### Statistical analyses

The primary efficacy endpoint will be the proportion of patients with at least one MAE in the study groups during the study period of 90 days. Conclusions from this study will be based on analyses conducted under the principle of intention-to-treat. For primary outcome, The Lan-DeMets spending function with O’Brien-Fleming type boundaries will be employed to preserve the overall two-sided type I error rate at the 0.05 significance level. The main conclusions of the study on primary outcome will be based on Fisher’s exact test between the treatment groups. The exact boundary values are *p* = 0.00132 in the interim analysis and *p* = 0.04868 in the final analysis.

For the primary outcome variable and for MACE and AKI incidence of the secondary outcomes, a time-to-event analysis will also be performed. The timing of MAEs is classified into four categories: 1) in the operating theatre, 2) in the intensive care unit, 3) during the primary stay at the ward of Meilahti hospital, and 4) after the primary stay at Meilahti hospital during the 90-day follow-up period.

For secondary outcomes, the proportions are compared with Fisher’s exact text and logistic regression models. For continuous variables, *t*-test and linear regression models will be used to evaluate differences between the treatment groups. All the analyses regarding the secondary outcomes will be conducted with a two-sided significance level of 0.05. No correction for the significance level will be done due to multiple testing.

Subgroup analyses will be conducted by preoperative glomerular filtration rate (GFR), EuroScore, and operation type. For GFR and EuroScore, the patients will be divided into two groups: those with a value higher and those with a value lower than the median value. For operation type, the patients will be divided into those operated on for aortic valve stenosis (including patient with other surgical corrections in addition to aortic valve stenosis) and those patients without correction of aortic valve stenosis.

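### At 693 per group, Fisher's exact test has about 78% power in the plan's own 50% v 42.5% scenario, not the stated 80% (minor)

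*Protocol article*

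**What the plan says.** All references are to the protocol article.

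- **Sample size analysis, original calculation.** The design was set "with a two-sided significance level α = 0.05, and power of 80"%. No other significance level is given in that section.
- **Sample size analysis, adaptation.** A review of the overall event rate was planned "in order to preserve the 80% power to detect a 7.5%-unit absolute difference between the study groups". The result was that "The MAE incidence after 550 patients was 42"%. Then "the assumption of 50% and 42.5% MAE incidence in the two study groups turned out to be the" least favourable case, "the highest needed patient number) with an estimate of 693 patients required for both patient groups". The total follows directly: "the final adapted sample size will be 1250 + 136 = 1386". That is 2 × 693, with no margin added; patients whose primary endpoint cannot be assessed are to be replaced.
- **Patients.** "The patients will be allocated 1:1 into the two study groups".
- **Statistical analyses.** "The main conclusions of the study on primary outcome will be based on" Fisher's exact test, with p-value boundaries of 0.00132 at the interim and 0.04868 at the final analysis.

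The article does not say which test or formula produced 693, and nothing in it links that number to Fisher's test.

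**The concern.** A power statement holds only for the test that will be used. Fisher's exact test conditions on the total number of events. With binary data its attainable p-values are discrete, so its true type I error lies below the nominal level. That costs power relative to the chi-square test, for which normal-approximation formulas are built. If 693 came from such a formula, the stated 80% belongs to a different test from the one that decides the trial.

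What is at stake is limited but definite. Keeping 80% power was the stated purpose of the re-estimation and so of the 136 added patients. The rates, group size, power and test are all fixed in the article, so the mismatch is within the text and is not a detail left to an analysis plan.

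**Working it through.** **Inputs.** p1 = 0.50, p2 = 0.425, difference 0.075, two-sided α = 0.05, power 80%, 693 per group, overall rate 42% (Sample size analysis); 1:1 allocation (Patients); Fisher's exact test, final threshold 0.04868 (Statistical analyses).

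**Step 1: reproduce 693.** Normal approximation with pooled variance under the null and no continuity correction:

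n = [z₁₋α/₂ √(2 p̄ q̄) + z₁₋β √(p1 q1 + p2 q2)]² / (p1 − p2)²

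- p̄ = 0.4625, q̄ = 0.5375, so 2 p̄ q̄ = 0.49719 and its root is 0.70512.
- p1 q1 + p2 q2 = 0.25 + 0.244375 = 0.494375, with root 0.70312.
- n = (1.95996 × 0.70512 + 0.84162 × 0.70312)² / 0.005625 = 3.8957 / 0.005625 = 692.6, so **693**.

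Other formulas with the same inputs:

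| Formula | n per group |
|---|---|
| Pooled, uncorrected, α = 0.05 | 693 |
| Arcsine, α = 0.05 | 693 (692.4) |
| Unpooled, α = 0.05 | 690 |
| Pooled, uncorrected, α = 0.04868 | 699 |
| Continuity-corrected, α = 0.05 | 719 |
| Continuity-corrected, α = 0.04868 | 725 |

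The two formulas that return 693 use α = 0.05 and make no allowance for Fisher's test. The continuity-corrected formula, the usual approximation to Fisher's test, gives a larger number.

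**Step 2: exact power at 693 per group.** For every pair of event counts (x, y) from 0 to 693, the two-sided p-value is computed. The binomial probabilities of all pairs at or below the threshold are then summed:

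power = Σ Bin(x; 693, p1) × Bin(y; 693, p2) over rejected (x, y)

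| True rates | Fisher, 0.05 | Fisher, 0.04868 | Chi-square, 0.04868 |
|---|---|---|---|
| 50% v 42.5% (design scenario) | 78.3% | **78.3%** | 79.85% |
| 45.75% v 38.25% (centred on 42%) | 79.3% | 78.7% | 80.2% |
| 42% v 34.5% | 80.5% | 80.4% | 81.9% |

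**Step 3: where the loss comes from.** In the design scenario, Fisher's power is 78.299% at 0.05 and 78.297% at 0.04868, so the threshold costs 0.002 points. The cause is the test's conservatism. With equal true rates between 34% and 55%, Fisher's actual size at 0.04868 is 0.042 to 0.044 (0.0433 at 46.25%). The chi-square test at the same threshold has size 0.048 to 0.050 and does not exceed 0.050.

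**Step 4: the interim look.** Two million simulated trials, with Fisher's test at 300 per group (p ≤ 0.00132) and then at 693 per group (p ≤ 0.04868), give overall power of 78.3%. The interim neither repairs nor worsens the figure.

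**Step 5: size needed for 80%.** Fisher at 0.04868, 50% v 42.5%: 79.35% at 719 per group, 79.9% at 725, 80.0% at **726**, 80.2% at 728. That is 726 − 693 = 33 more per group, or 66 in total (about 5%).

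**The case against.** The strongest reply is that this is small and conventional. Sizing with a normal approximation and analysing with Fisher's test is common, and the mismatch errs on the safe side for type I error. The loss is 1.7 points in a scenario that the plan itself calls its least favourable. At 42% v 34.5% Fisher's power is 80.4%, and for a difference of 7.7 points (50% v 42.3%) it is also 80.4%. The article condenses a fuller protocol, which may name the sizing method. All of this stands, and it makes the point minor. It does not make the 80% correct for the stated test in the stated scenario.

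Three stronger readings are tempting, and the document does not support them.

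- **That 693 is an arithmetic error.** It is not: 693, 136 and 1386 all reproduce. That 693 is a chi-square figure is inferred from the match, and the arcsine formula fits equally well.
- **That the lower final threshold causes the shortfall.** At 50% v 42.5% it costs nothing measurable. At 45.75% v 38.25% it costs about 0.6 points (79.3% to 78.7%), but that is not the scenario on which 693 rests. Nothing here shows the stated boundary to be wrong.
- **That calling 50% v 42.5% the worst case is false.** Over all possible rates, the largest number for a 7.5-point difference is 697 (53.75% v 46.25%), only 4 more per group. The phrase follows a blinded rate of 42% and may refer to rates near it. The article does not say, so an error is not established.

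There is also a fair objection to changing the primary test. Under Trial status, 1143 patients are already enrolled, beyond the 600 needed for the interim analysis, which uses the same test. Moving to a less conservative test at that stage needs a better reason than 1.5 points of power.

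**Conclusion.** The point holds as a minor mismatch between the sizing and the primary test. With Fisher's exact test, 693 per group gives 78.3% power for 50% v 42.5%, about 1.7 points below the stated 80%. At rates centred on the observed 42% it gives 78.7%. Essentially all of the loss in the design scenario comes from the conservatism of Fisher's test.

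This rests on the article's own rates, group size, test and threshold, on equal groups of 693 assessable patients, and on the usual two-sided Fisher p-value (summing all tables no more probable than the one observed). The source of 693 is inferred, but the power figure does not depend on that inference. Type I error is not at risk.

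**What to change.** **Preferred:** keep Fisher's test and correct the power statement. Under Sample size analysis, say that 693 per group gives about 78% power for 50% v 42.5% with Fisher's exact test at the stated final threshold, and about 79% at rates centred on the observed 42%. Name the formula that produced 693. This costs one or two sentences.

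**Alternative, only before unblinding:** name the chi-square test without continuity correction as primary at the stated final threshold (exact power 79.85% for 50% v 42.5%, actual size at most 0.050), or an unconditional exact test. Keep Fisher's test as a sensitivity analysis. This adds no patients, but it changes the primary analysis late in the trial, so it should be a dated amendment with its reason stated. It is the more debatable route.

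Enlarging the trial by 66 patients to reach 80% with Fisher's test is not warranted for a shortfall of this size.

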### Statistical analyses

The primary efficacy endpoint will be the proportion of patients with at least one MAE in the study groups during the study period of 90 days. Conclusions from this study will be based on analyses conducted under the principle of intention-to-treat. For primary outcome, The Lan-DeMets spending function with O’Brien-Fleming type boundaries will be employed to preserve the overall two-sided type I error rate at the 0.05 significance level. The main conclusions of the study on primary outcome will be based on Fisher’s exact test between the treatment groups. The exact boundary values are *p* = 0.00132 in the interim analysis and *p* = 0.04868 in the final analysis.

For the primary outcome variable and for MACE and AKI incidence of the secondary outcomes, a time-to-event analysis will also be performed. The timing of MAEs is classified into four categories: 1) in the operating theatre, 2) in the intensive care unit, 3) during the primary stay at the ward of Meilahti hospital, and 4) after the primary stay at Meilahti hospital during the 90-day follow-up period.

For secondary outcomes, the proportions are compared with Fisher’s exact text and logistic regression models. For continuous variables, *t*-test and linear regression models will be used to evaluate differences between the treatment groups. All the analyses regarding the secondary outcomes will be conducted with a two-sided significance level of 0.05. No correction for the significance level will be done due to multiple testing.

Subgroup analyses will be conducted by preoperative glomerular filtration rate (GFR), EuroScore, and operation type. For GFR and EuroScore, the patients will be divided into two groups: those with a value higher and those with a value lower than the median value. For operation type, the patients will be divided into those operated on for aortic valve stenosis (including patient with other surgical corrections in addition to aortic valve stenosis) and those patients without correction of aortic valve stenosis.

The safety analysis is based on comparison of serious adverse events (SAE) between the study groups. Due to its nature, a MAE is always also a SAE. However, a MAE is not reported as a SAE in order to avoid double reporting. Consequently, the final number of SAEs is the sum of MAEs and the events reported as a SAE. Because a single patient may have more than one SAE, three different statistical analyses will be conducted for evaluation of study safety:
The number of patients with at least one SAE using Fisher’s exact testThe SAE number per a patient within those study patients with at least one SAE using *t*-testThe SAE number per a patient within all study patients using *t*-test

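### The primary test is an unadjusted Fisher's exact test, valid but inefficient; a prespecified analysis adjusted for EuroScore, preoperative GFR and operation type would restore 80% power and may add more

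*Protocol article*

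**What the plan says.** The Statistical analyses section of the protocol article fixes the primary test: "The main conclusions of the study on primary outcome will be based on Fisher’s exact test between the treatment groups". The significance threshold is "0.04868 in the final analysis".

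The same section lists preoperative GFR, EuroScore and operation type as subgroup factors. GFR and EuroScore are each cut into "those with a value higher and those with a value lower than the median value". Operation type is divided by whether aortic valve stenosis is corrected. Regression models are planned for secondary outcomes and a time-to-event analysis for the primary outcome, in both cases without named covariates. The Randomization section describes blocks tied to production lots and states no stratification by risk.

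The Sample size analysis section aims "to detect a 7.5%-unit absolute difference between the study groups in the primary outcome measure" with a "two-sided significance level α = 0.05, and power of 80" per cent. After a blinded look at the event rate it adopts "the assumption of 50% and 42.5% MAE incidence in the two study groups" as the most demanding case. This gives 693 per arm and 1386 in all.

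**The concern.** EuroScore is a risk score, GFR bears directly on the kidney component of MAE, and the sponsor thought all three factors important enough to define subgroups. If they predict MAE, an unadjusted 2x2 test leaves the variation they explain as noise. As no risk stratification is stated, it also leaves chance imbalance in risk between the arms uncorrected.

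At stake is power. The trial was enlarged by 136 patients to hold 80%. If the test named for the main conclusion does not reach 80% at that size, and baseline data already planned for use could recover the loss, the primary analysis is a less efficient choice than it need be.

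A lesser matter is the median split of two continuous variables, which discards information when the question is whether the treatment effect varies with risk.

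**Working it through.** **1. Reproduce the stated sample size.** Inputs from the Sample size analysis section: 50% v 42.5%, two-sided 0.05, power 80%. With the pooled-variance formula and no continuity correction:

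n = [1.960·√(2·0.4625·0.5375) + 0.8416·√(0.5·0.5 + 0.425·0.575)]² / 0.075²
= [1.3820 + 0.5918]² / 0.005625 = 692.6, so **693 per arm**, as stated.

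The original 621 also follows from an unadjusted two-proportion formula (30% v 37.5%, unpooled variance). So 693 is the size for an unadjusted z or chi-square test at 0.05. It is not the size for Fisher's test at 0.04868.

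**2. Power of the planned test, without any covariate assumption.** 693 per arm, 50% v 42.5%:

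| Test | Threshold | Power |
|---|---|---|
| Unadjusted z | 0.05 | 80.0% |
| Unadjusted z | 0.04868 | 79.7% (exact chi-square 79.8%) |
| Fisher, exact enumeration | 0.04868 | **78.3%** |

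The gap to target is 80.0 − 78.3 = 1.7 points. About 0.3 comes from the final boundary (80.0 to 79.7) and about 1.4 from Fisher's conservatism (79.7 to 78.3). At 45.75% v 38.25%, which averages the observed 42%, Fisher's power is 78.7%. The test's true two-sided size at 0.04868 is 0.042 at a common rate of 42% and 0.044 at 50%.

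**3. Gain from adjustment.** The article gives no prognostic strength for the three factors, so it has to be assumed and varied.

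(a) Approximation: if the covariates explain a share R² of outcome variance, the effective size is 693/(1 − R²) per arm. For example, R² = 0.10 gives 693/0.90 = 770. Power at 0.04868:

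| R² | 0 | 0.02 | 0.05 | 0.10 | 0.15 |
|---|---|---|---|---|---|
| Power | 79.7% | 80.5% | 81.7% | 83.7% | 85.7% |

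(b) Simulation: logit P(MAE) = arm intercept + s·x, where x is standard normal and stands for the three factors combined, with intercepts set to give 50% and 42.5% overall. There were 6000 runs (Monte Carlo SE about 0.5 points) and every test used 0.04868. The Fisher column is a continuity-corrected chi-square, which behaves like Fisher.

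| s | AUC | Fisher-like | Unadjusted z | Adjusted logistic | Adjusted minus z |
|---|---|---|---|---|---|
| 0.37 | 0.60 | 78.4% | 79.9% | 80.9% | 1.0 |
| 0.57 | 0.65 | 78.6% | 80.0% | 82.8% | 2.7 |
| 0.80 | 0.70 | 78.7% | 80.3% | 84.8% | 4.5 |
| 1.05 | 0.75 | 78.0% | 79.4% | 86.9% | 7.5 |

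Fisher and z depend only on the overall rates, so their movement down the table is simulation noise. Against a steady 80%, the covariates add about 1 point at AUC 0.60 to 0.62 and about 7 at 0.75. With an uninformative covariate the adjusted model gives about 80%.

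**4. Type I error.** With both arms at 46.25% and s = 0.80 (8000 runs), the adjusted test rejected in 4.79% of trials at nominal 4.868%. The Fisher-like test rejected in 4.25%.

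**5. Median split.** For a normally distributed covariate with a linear interaction, a median split keeps 2/π = 0.64 of the information, a loss of about 36%. The article supports neither condition, so this is only a guide.

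**The case against.** The strongest reply is that nothing here is wrong. Fisher's test is a valid test of the stated endpoint. The sample size is also that of an unadjusted comparison, so design and test agree in using no covariates, and no stratification factor is stated that the model would have to include. All of this stands: the point is about efficiency.

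Second, a reader might infer that power falls below 80% because covariates are left out. Section 2 of the working does not support that. Nearly all of the shortfall disappears with an unadjusted chi-square test.

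Third, a reader might infer that adjustment is bound to deliver a large gain. The article gives no figure for how well these factors predict a nine-component MAE, and with weak factors the covariate gain is close to nil.

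Fourth, a reader might think adjustment is free. A logistic model yields a conditional odds ratio, whereas the trial is sized on an absolute difference, so a standardisation step is needed. The Interim analysis section ties the interim look to the same Fisher comparison. At submission 1143 of 1386 patients were enrolled, so a change would come late.

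Finally, the article condenses a fuller plan. The factors are confined to subgroups in what the article names, but an analysis plan not shown may contain a supportive adjusted analysis. That does not remove the point, because the article itself fixes which test carries the main conclusion.

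**Conclusion.** The point holds as a recommendation to use a more efficient primary analysis. It is not a finding of error.

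- **Firm:** the named test has 78.3% power at the design's own rates and final boundary, 1.7 points under target, with a true size of about 0.042 to 0.044. This needs no outside assumption.
- **Nearly firm:** moving to a logistic (or chi-square) test brings power back to about 80%, even if the covariates contribute nothing.
- **Conditional:** adjustment adds roughly 1 to 7 further points if the combined baseline AUC for MAE is about 0.62 to 0.75. The simulation also assumes that a single normal score summarises the three factors and enters the model in the right form.

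The documents do not support calling the Fisher test invalid, attributing the shortfall to missing covariates, or promising a particular gain. The median-split issue is minor, because the subgroup analyses do not carry the primary conclusion.

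**What to change.** Before unblinding, by a documented amendment made without knowledge of allocation:

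1. Make the primary analysis a logistic model with treatment, EuroScore (continuous), preoperative GFR (continuous) and operation type (aortic valve stenosis corrected or not).
2. Test treatment at the stated final boundary, 0.04868.
3. Report the standardised risk difference with confidence interval, so the result stays on the scale of the 7.5-point target.
4. Keep Fisher's exact test as a sensitivity analysis.
5. As a lesser addition, test treatment-by-EuroScore and treatment-by-GFR interactions on the continuous values, and keep the median-split subgroups for display.

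If the primary test can no longer be changed, prespecify the adjusted risk difference as the main supportive analysis.

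No new data are needed. The covariate form and the handling of missing baseline values must be fixed in advance. The amendment should also state openly that the interim look is specified with Fisher while the final test is adjusted. The Unblinding section keeps the code with the hospital pharmacy and the analysing statistician blind to treatment, so an allocation-blind amendment is feasible.

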### Interim analysis

One interim analysis will be conducted after 600 patients have been recruited and followed for 90 days. The principle of intention-to-treatment will be followed in all group comparisons of the interim analysis. The primary efficacy analysis (MAE) and safety analysis (MAE + SAE) will be conducted as described in the “Statistical analyses” section above.

The Data and Safety Monitoring Board will recommend pausing or stopping the trial if group difference in the primary outcome measure (proportion with at least one MAE) is found to be statistically significant at group sequential monitoring boundaries using Lan-DeMets spending functions. The exact boundary value for the interim analysis is *p* = 0.00132.

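### All stated safety comparisons use MAEs plus SAEs combined, so a difference in serious events outside the MAE list can be heavily diluted or offset; a separate comparison should be added

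*Protocol article*

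**What the plan says.** The Statistical analyses section of the protocol article sets the basis for safety: "The safety analysis is based on comparison of serious adverse events (SAE) between the study groups". It treats every MAE as an SAE by nature but keeps the two reporting streams apart: "However, a MAE is not reported as a SAE in order to avoid double reporting". The two are added back together for analysis: "Consequently, the final number of SAEs is the sum of MAEs and the events reported as a SAE".

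The section then says that "three different statistical analyses will be conducted for evaluation of study safety". These are:
- patients with at least one SAE (Fisher's exact test);
- SAEs per patient among those with at least one (t-test);
- SAEs per patient among all patients (t-test).

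Under the definition above, all three use the summed count. The Interim analysis section carries this over: "The primary efficacy analysis (MAE) and safety analysis (MAE + SAE) will be conducted as described in the “Statistical analyses” section above".

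MAEs are also compared on their own, as the primary outcome and as a total count among the secondary outcomes. For the separately reported SAEs on their own, the article states no between-group comparison.

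**The concern.** The sum is dominated by the primary efficacy endpoint. The Sample size analysis section reports, in per cent: "The MAE incidence after 550 patients was 42". That figure covers both arms with the allocation code unbroken.

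In the first safety test, a patient who already has an MAE adds nothing when another serious event follows. Only patients whose sole serious event lies outside the MAE list move the proportion. In the two count tests, MAEs add variance that has nothing to do with the other events.

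Two things can follow. A real difference in serious events outside the MAE list (a serious allergic reaction, for example) can be diluted until it is unlikely to be detected. And if albumin lowers MAEs, as the trial hypothesises, the fall in MAEs can outweigh a rise in other serious events, so that the summed comparison favours albumin. Safety is in the trial's title and is reviewed at the interim, so a comparison that separates these events from efficacy is worth having.

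**Working it through.** **Inputs from the article.** 693 per group, two-sided α = 0.05, 80% power, adapted rates 50% vs 42.5%, design effect 7.5 points, observed MAE incidence 42%, interim at 600 patients (about 300 per group at 1:1).

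**Assumed inputs.** The rate of non-MAE SAEs and their overlap with MAEs are not given, so ranges are used.

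**Step 1: reproduce the plan's figure.** The two-proportion formula with pooled null variance and no continuity correction gives 693 per group for 50% vs 42.5%, with power 80.0%. This matches, so the same formula is used below:

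power = Φ[(|p₁ − p₀| − 1.96·√(2p̄(1 − p̄)/n)) / √((p₀(1 − p₀) + p₁(1 − p₁))/n)].

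**Step 2: dilution with MAEs equal.** If a fraction m of patients has an MAE and, independently, a fraction s has another SAE, the summed proportion is m + s − ms. With m = 0.42:
- s = 0.05 gives 0.42 + 0.05 − 0.021 = 0.449;
- s = 0.10 gives 0.42 + 0.10 − 0.042 = 0.478.

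A 5-point difference becomes 2.9 points on a base near 45%. For 5% vs 10% alone, power = Φ[(0.05 − 1.96 × 0.01415)/0.01409] = Φ(1.58) = 94%. For the sum, power = Φ[(0.029 − 1.96 × 0.02679)/0.02678] = Φ(−0.88) = 19%.

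| Other SAEs (assumed) | Summed proportions | Power alone | Power summed |
|---|---|---|---|
| 2% vs 5% | 43.2% vs 44.9% | 86% | 10% |
| 5% vs 8% | 44.9% vs 46.6% | 62% | 10% |
| 5% vs 10% | 44.9% vs 47.8% | 94% | 19% |
| 10% vs 16% | 47.8% vs 51.3% | 91% | 25% |
| 20% vs 27% | 53.6% vs 57.7% | 87% | 33% |

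Simulating Fisher's exact test for 5% vs 10% gives 94% alone and 18% summed. Eighty per cent power would need 435 per group alone and 4641 per group summed.

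**Step 3: sensitivity to overlap (5% vs 10%).** Let f be the share of patients with another SAE who also have an MAE; the summed proportion is 0.42 + s(1 − f).
- f = 0: 47% vs 52%, power 46%.
- f = 0.42 (independence): 19%.
- f = 0.6: 44% vs 46%, power 11%.
- f = 0.8: 43% vs 44%, power 6%.

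The loss does shrink when these events are common and never overlap with MAEs: 20% vs 27% with f = 0 gives 62% vs 69% and power 78%, against 87% alone.

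**Step 4: interim.** With 300 per group and 5% vs 10%, power at two-sided 0.05 is 64% alone and 11% summed (independence).

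**Step 5: count tests.** Taking other SAEs as Poisson and the variance of the MAE count as 0.55 to 1.1 (both assumed), power for 5% vs 10% on the all-patient count is about 95% alone and 15% to 25% summed.

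**Step 6: offset.** Place the 7.5-point design effect around 42%, i.e. 45.75% on Ringer and 38.25% on albumin, and let other SAEs double from 5% to 10% on albumin:
- Ringer: 0.4575 + 0.05 − 0.4575 × 0.05 = 48.5%;
- albumin: 0.3825 + 0.10 − 0.3825 × 0.10 = 44.4%.

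The sum favours albumin by 4.0 points. The two effects would cancel exactly only if other SAEs rose from 5% to about 16.5%, or from 10% to about 21%.

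**The case against.** **The sum is not an error.** MAEs are serious events, and because they are not reported as SAEs, leaving them out would understate total serious harm. This stands: the sum should be kept.

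**The full protocol or analysis plan may tabulate SAEs separately.** It may. But the article does not leave the safety analysis open. It defines the variable, lists three tests and repeats the definition for the interim. The point is about that stated choice.

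**Much harm is already visible elsewhere.** Acute kidney injury, blood loss, each blood product, MACE and 90-day mortality are separate secondary outcomes tested at 0.05 without multiplicity correction. Infection, stroke and major bleeding are MAE components, and putative SUSARs have their own unblinding route. This also stands. A reader might infer that the plan has almost no ability to show harm distinct from efficacy; these comparisons rule that out. The gap is confined to serious events outside the MAE list and outside those outcomes.

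**The information can be recovered.** Total MAEs subtracted from total SAEs gives the reported SAEs per arm, and in the offset case a 7.5-point MAE difference beside a 4.0-point difference in the sum would be a clue. This is partly right. Subtraction gives events, not patients with at least one, and no planned test of the difference.

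**The rates are assumed, and rare events would be missed anyway.** At 693 per arm, a doubling analysed alone has power of only 19% (0.5% vs 1%), 33% (1% vs 2%) or 59% (2% vs 4%). This stands as a limit on what the fix can deliver, though the sum does worse in each case.

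**Conclusion.** The point holds in a limited form. The article's stated safety comparisons, at the interim and the end, all use MAEs plus reported SAEs, and none isolates the non-MAE SAEs. With MAE incidence near 42%, a difference confined to those events can be heavily diluted: for assumed rates of 5% vs 10%, power falls from 94% to 19% under independence and to about 46% even with no overlap. If albumin lowers MAEs by the design effect, the sum can point the other way.

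A reader might go further and infer that a safety signal is bound to be swamped. The documents do not support that: they give neither the rate of non-MAE SAEs nor their overlap with MAEs, and 42% is a blinded figure from the first 550 patients. Dilution appeared in every case tried, but its size rests on these assumptions. The change is worth making because it costs little; nothing here invalidates the sum or the primary analysis.

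**What to change.** In the Statistical analyses and Interim analysis sections, add one pre-specified between-group comparison: patients with at least one SAE that is not an MAE, together with the number of such events. Report it at the interim and final analyses beside the existing MAE + SAE sum.

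No new data are needed, because MAEs are not reported as SAEs and the non-MAE SAEs are already a separate data stream. The cost is one more safety comparison. It will have low power if these events are rare, so it should be read as an estimate with its confidence interval, and a non-significant result should not be taken as evidence of safety.
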